### Statistical analysis

Descriptive statistics will be used to characterize the entire population and subgroups of interest at baseline and follow-up. Summary statistics such as means, medians, standard deviations and ranges will be used to describe continuous variables, and frequencies will be tabulated for categorical variables. For outcomes collected longitudinally, Kaplan Meier survival curves, scatter plots and grouped box plots will be used to examine assumptions of survival free of adverse outcome or relapses, and linearity and symmetry of data. Repeated measures analysis will be applied for data derived at multiple time points for same child to study correlation with extent and duration of proteinuria. Cox regression analysis will be applied to analyze the time to event data of the primary or secondary endpoints collected in both cohorts of NS and healthy children and assess association of the outcome hazard with clinical covariates of interest. Correlation of markers of endothelial dysfunction and cIMT will be done with extent and duration of proteinuria as defined by the status of remission and number of relapses per year. cIMT will be used as the gold standard for subclinical vasculopathy for evaluation of association with progression of endothelial function. IMT is chosen for diagnostic evaluation study for other biomarkers of cardiovasculopathy since it is the most well characterized surrogate marker of subclinical atherosclerosis. *P*-value < 0.05 will be considered as significant. Statistical analysis will be performed using SPSS Version 17.0.

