#### Cohort B: Healthy controls

Healthy siblings of the recruited children with NS between 1 and 18 years age. Children will be deemed healthy only if normotensive, with eGFR > 60 ml/min/1.73 m2 and with no systemic illness or serious bacterial illness in the preceding 12 weeks.A detailed phenotyping of the disease profile and exposure to cardiovascular risk factors will be done for each child using a combination of clinical and laboratory examination. In addition a detailed nutritional assessment including dietary recall will be done in each child. Routine case specific laboratory assessments for clinical management of an individual case will continue as per standard treatment guidelines of Indian Society of Pediatric Nephrology [16, 17].Baseline assessment of functional aberrations in microvascular and macrovascular endothelium will be done using LDF for cutaneous PORH and B-mode ultrasound for brachial artery FMD respectively.Baseline screening for cardiovascular comorbidity will be done using 2D-echocardiography, high-resolution ultrasonography of carotid arteries and NFC.In case of child being in relapse at the time of recruitment, a repeat assessment will occur at 12 weeks after the baseline assessment. Comparison of FMD and PORH between relapse and remission in same child will assess any short term effect of disease activity on these parameters.

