For the phase 2 of study with prospective follow up for progression of endothelial dysfunction towards subclinical atherosclerosis as determined by cIMT as the gold standard, if total of 95 children (NS and controls) were to be followed for 24 months after an accrual period of 12 months, assuming a median time of 12 months for a detectable difference of cIMT of > 0.004 mm over 12 months between children with NS and healthy controls, the probability is 80% that the study will detect a difference at a two sided 5.0% significance level, if the true hazard ratio is 2.0. With these preceding assumptions again minimum of 50 children with NS and 50 healthy controls will need to be recruited and followed up over 24 months.

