### Strategies to minimize losses to follow-up

All the patients will be followed up at 12 and 24 months after the baseline assessments. To minimize the risk of retrieval bias, two to five telephone numbers (both mobile and landline) along with their army service number will be noted from the patients or his/her relatives at the time of recruitment. A trained research worker will attempt to contact the participants one month, one week and two days prior to their respective follow up.

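### Cox regression is planned for endpoints determined only at scheduled visits; the event times are interval-censored, and the power lost (about 1 to 45 points) depends on choices the plan does not state

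*Protocol article*

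**What the plan says.** The Statistical analysis section names the model: "Cox regression analysis will be applied to analyze the time to event data of the primary or secondary endpoints collected in both cohorts". It also plans Kaplan-Meier curves, and a repeated-measures analysis whose stated purpose is correlation with proteinuria. It adds "Statistical analysis will be performed using SPSS Version 17.0" and gives no rule for ties or for coding event time.

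The schedule is in the section on losses to follow-up: "All the patients will be followed up at 12 and 24 months after the baseline assessments". The abstract gives the same two follow-up times, and the Phase II section collects blood and urine at baseline, 12 and 24 months. There is one extra assessment. For a child in relapse at recruitment, "a repeat assessment will occur at 12 weeks after the baseline assessment", to compare FMD and PORH between relapse and remission.

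Part B of the sample-size section plans Phase II on the hazard-ratio scale, for a cIMT event with a median of 12 months and 95 children in total: "the probability is 80% that the study will detect a difference at a two sided 5.0% significance level, if the true hazard ratio is 2.0".

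**The concern.** A change in FMD, PORH or cIMT is found when the child is scanned. If it is present at 24 months and was absent at 12, all that is known is that it arose in between. The Cox partial likelihood uses the order of event times and is built for times that are exact and largely untied. Here the times are either two heavily tied values (12 and 24) or appointment dates, whose order within a visit says nothing about the order of progression.

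Phase II is planned to detect a hazard ratio of 2.0 with 80% power. If the fitted model estimates something smaller, or ranks children by appointment, neither the reported hazard ratio nor the power matches that plan. The sample-size section makes no allowance for this.

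**Working it through.** **Inputs.** Hazard ratio 2.0, two-sided 5%, power 80%, 95 children, 12 months of accrual plus 24 of follow-up, median 12 months (sample-size section, part B); visits at 12 and 24 months. The group with the 12-month median is not named, so both readings are run: A, NS 12 and control 24 months; B, control 12 and NS 6. Exponential event times are assumed.

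**1. The plan's own figure.** Events needed = 4(1.960 + 0.842)² / (ln 2)² = 65.35. With uniform accrual, P(event) = 1 − [exp(−24λ) − exp(−36λ)] / (12λ), where λ = ln 2 / median. Reading A gives 0.820 and 0.577, mean 0.6986, so N = 65.35 / 0.6986 = 93.5, and power at 95 is 80.6%. Reading B gives N = 73. The stated 95 is thus reproduced under reading A by a formula that treats event times as observed exactly.

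If each child is followed for 24 months only, the mean event probability under A is (0.75 + 0.50) / 2 = 0.625 and power at 95 is 76%. That is a separate matter, but it is why the benchmarks under A below are near 75%.

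**2. What the visits show (48 NS, 47 controls).**
- A: month 12, 48 × 0.5 + 47 × 0.293 = 37.8 events; month 24, 24 × 0.5 + 33.2 × 0.293 = 21.7.
- B: month 12, 48 × 0.75 + 47 × 0.5 = 59.5; month 24, 12 × 0.75 + 23.5 × 0.5 = 20.75.

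All events fall on two distinct times.

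**3. What each model estimates.** Let p₁ and p₀ be the per-interval risks in NS and control children. They are the same in both intervals here. With Breslow ties, the expected score equation at each visit, n₁p₁ = (n₁p₁ + n₀p₀) · n₁θ / (n₁θ + n₀), solves to θ = p₁/p₀. That is a risk ratio: 0.5/0.293 = 1.71 (A) and 0.75/0.5 = 1.50 (B). The complementary log-log model estimates ln(1 − p₁) / ln(1 − p₀), which is 2.0 in both.

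**4. Type I error with Breslow ties.** The Breslow variance omits the factor (n − d)/(n − 1), roughly 1 minus the per-interval risk. With equal hazards the test statistic has standard deviation √0.5 = 0.707 (median 12 in both groups) or √0.707 = 0.841 (median 24). The rejection rates are P(|Z| > 2.77) = 0.6% and P(|Z| > 2.33) = 2.0%, in line with the simulation.

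**5. Simulation, 48 + 47 children, nominal 12/24 coding, 3,000 data sets per scenario.**

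| Model | Power, A | Power, B | Type I error, median 24 / 12 |
|---|---|---|---|
| Cox, Breslow | 53.0% | 38.9% | 1.6% / 0.3% |
| Cox, Efron | 73.5% | 81.6% | 4.2% / 4.3% |
| Complementary log-log | 74.6% | 84.3% | 4.5% / 5.0% |
| Cox, exact times (not observable) | 75.1% | 87.0% | 4.5% / 5.0% |

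Against the complementary log-log model, Breslow loses 21.6 (A) and 45.4 (B) points; Efron loses 1.1 and 2.7.

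**6. Actual visit dates, equally timed in both groups.** A separate simulation of the same size gives 67% against 76% (A) and 73% against 86% (B), a loss of 9 and 13 points. At 50 + 50 children, type I error with this coding is 4.6–4.7%.

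**7. Larger follow-up.** With 140 NS children and 70 controls, Breslow power is 86.9% against 96.4% with exact times (A) and 79.7% against 99.2% (B), a loss of 9.5 and 19.5 points.

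**8. Unequal visit timing (hypothetical).** With actual dates and equal hazards, scanning NS children earlier than controls gives type I error of 11–13% (one week), 22–30% (two weeks) and 44–65% (one month). The 12-week repeat alone, in 30–50% of NS children, leaves it at or below 5%.

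**The case against.** The strongest reply is that a competent run of the planned model may do almost no harm. With nominal visit times and Efron ties it is within about 3 points of the grouped-time model and holds its error rate. That stands. So does the remark that tie handling and time coding are commonly left to an analysis plan, so their absence from the article is no fault. The point here is narrower: the article names a model and a visit schedule, and the two do not fit.

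Two stronger readings are tempting, and the article supports neither.
- A reader might infer that the trial will lose 20 to 45 points of power. That needs Breslow ties. The article names a software package but no tie method, so Breslow is an assumption.
- A reader might infer that the test will reject falsely. That needs a systematic difference in visit timing between groups. The article describes none: controls are siblings of the cases, and one reminder schedule is given for all participants.

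Other limits also stand. Progression over 24 months is a secondary objective. Relapse, which the same section mentions for survival curves, can be dated, and Cox suits it. The larger planned cohort softens the loss. The simulations assume that an event is recognised without error at each visit, so they compare models and do not forecast this trial's power.

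**Conclusion.** The point holds as a mismatch between the named model and the stated visits. The size is conditional. At about 95 children and a true hazard ratio of 2.0, the loss against a grouped-time model is about 1–3 points (nominal times, Efron), 9–13 points (actual dates, equal timing) or 21–45 points (nominal times, Breslow). In the Breslow case the hazard ratio shrinks to about 1.5–1.7 and type I error falls to roughly 0.2–1.8%. If all 140 NS children and 70 controls are followed, the Breslow loss is about 10–20 points. False rejection is a risk only under unequal visit timing.

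These figures rest on exponential times, two readings of the 12-month median, and assumed tie and coding rules. Because the result turns on choices not yet stated, the model should be settled before analysis.

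**What to change.** In the Statistical analysis section:
- Keep Cox regression for outcomes with a known date, such as relapse, clinical events or death.
- For every endpoint determined at scheduled visits, specify a grouped-time proportional-hazards model: binary regression with complementary log-log link, one indicator per scheduled visit, group and the planned covariates. An equivalent interval-censored model would also serve. The group coefficient is the log hazard ratio on which Phase II is sized.
- Present Kaplan-Meier curves for these endpoints as cumulative proportions by scheduled visit.

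This changes analysis wording only, with no new children, visits or measurements. The small cost is that children scanned well outside the visit window need an offset for interval length or a sensitivity analysis.

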### Strategies to minimize losses to follow-up

All the patients will be followed up at 12 and 24 months after the baseline assessments. To minimize the risk of retrieval bias, two to five telephone numbers (both mobile and landline) along with their army service number will be noted from the patients or his/her relatives at the time of recruitment. A trained research worker will attempt to contact the participants one month, one week and two days prior to their respective follow up.

### Outcomes and their measurement

The expected outcomes of the CVONS study will able to assess extent of impairment in macrovascular & microvascular endothelial function due to childhood NS in the absence of usual confounders in adults like smoking, alcohol, coronary heart disease, diabetes. This study may able to delineate progression of endothelial dysfunction in relation to - disease activity (extent and duration of proteinuria) and structural markers of subclinical atherosclerosis (cIMT). It may provide preliminary normative data for Indian children for vascular measurements. It may also provide correlation of cardiovascular risk factors with endothelial dysfunction and subclinical atherosclerosis for pediatric cardiovascular risk stratification in nephrotic syndrome.

## Discussion

This study aims to provide a better understanding of the epidemiology of endothelial dysfunction and associated subclinical cardiovascular co-morbidity in childhood NS. We hypothesize functional as well as structural alterations in the entire microvascular, macrovascular and cardiac endothelium due to NS and seek to evaluate the same using a combination of noni-nvasive imaging, biochemical and flow cytometry based biomarkers. Amongst the imaging biomarkers, our study may encounter certain challenges during the use of LDF, RF-IMT and FMD. During the procedure of LDF, subjects are restricted to immobilized to get the accurate cutaneous perfusion flux. It is notable that LDF does not provide a direct measurement of blood flow, but rather is an index of cutaneous perfusion [31, 32]. As yet there is no preliminary normative data on flux values as well as flux variation in proximal and distal vascular beds of forearm and we seek to obtain them from the controls. Seasonal temperature variation causing deviation in the flux values is obviated by measurements at uniform ambient temperature after a rest period. Short neck length in younger children in relation to the vascular probe makes assessment of the internal carotid artery (ICA) thickness difficult especially since the ICA tends to dip inwards in them [22, 23]. Repetitive swallowing prolongs the RFQIMT acquisition times. Carotid bifurcation and the inferior thyroid artery will form reference points for manual measurement of IMT. Data for objective assessment of nail fold capillaroscopy for non rheumatological disorders in childhood too remains sparse [25, 26].

FMD assessment is highly observer dependent and, variations in cuff placement/positioning have to be minimized. Visualization of brachial artery in young children can be difficult and there is a need to ensure measurement at same point in cardiac cycle. M-mode ultrasonography offers high spatial and temporal resolution and is therefore suitable for diameter measurement of pulsatile vessels. Till yet there is no any normative data for age related cut-off values for the diameter of brachial artery. Depending upon pulse pressure and vascular stiffness, arterial diameter may vary quite considerably across a single cardiac cycle. In some subjects, the change in diameter may be as much as one millimeter, which, if unaccounted for, may completely confound the assessment of FMD [33–35]. In our study we seek minute-wise sequential data pertaining to the flow mediated brachial artery parameters. Further FMD values obtained by M-mode and by the conventional B-mode ultrasonography on longitudinal images will be compared. M-mode brachial artery diastolic and systolic diameter measurement is feasible, suitable, and accurate for the assessment of FMD even without the need for electrocardiography.

Flow cytometry evaluation of endothelial progenitor cells, circulating endothelial cells and endothelial micro-particles is a challenge and pediatric data is lacking [11]. Scattered within the vascular wall, these cells participate in angiogenesis and vasculogenesis and support regeneration of epithelial cells and during the course of chronic cardiovascular and kidney disease they undergo premature senescence and fragmentation to generate endothelial micro-particles. No study till date has tried to correlate these novel cellular markers with imaging biomarkers of endothelial dysfunction.

Overall CVONS study will able to prospectively assess the extent of functional and structural impairment in macrovascular & microvascular endothelial function and the corresponding biochemical and cytological correlates due to childhood NS in the absence of usual confounders in adults like smoking, alcohol, coronary heart disease, diabetes. In the prospective phase, delineation of progression of endothelial dysfunction in relation to disease activity (extent and duration of proteinuria) and structural markers of subclinical atherosclerosis (cIMT) will be focused upon. Preliminary prospective normative data for Indian children for vascular measurements is sought to be generated. Better understanding of the epidemiology of endothelial dysfunction and associated subclinical cardiovascular co-morbidity in childhood NS is expected. Findings on characterization of prevalence of endothelial dysfunction and subclinical markers may be used to design future randomized controlled trials for evaluating the efficacy of preventive and therapeutic interventions in reducing the incidence of cardiovascular disease.

## Abbreviations

CAD: Coronary Artery Disease
CD: Cluster of Differentiation
CEC: Circulating Endothelial Cells
cIMT: Carotid Intima Media Thickness (cIMT)
CKD: Chronic Kidney Disease
CVONS: Cardiovascular Outcome in Nephrotic Syndrome
EPC: Endothelial Progenitor Cells
FACS: Fluorescence-Activated Cell Sorting
FITC: Fluorescein Isothiocyanate
FMD: Flow Mediated Dilation
IMT: Intima Media Thickness
KDR: Kinase insert Domain-conjugating Receptor
LDF: Laser Doppler Flowmetry
LDI: Laser Doppler Imaging
LV: Left Ventricle
LVMI: Left Ventricular Mass Index
NFC: Nail Fold Capillaroscopy
NO: Nitric Oxide
NOS: Nitric Oxide Synthethases
NS: Nephrotic Syndrome
PORH: Post Occlusive Reactive Hyperaemia
RF: Radiofrequency
SRNS: Steroid Resistant Nephrotic Syndrome
SSNS: Steroid Sensitive Nephrotic Syndrome
